## Exclusion criteria

◦ Uncontrolled concurrent malignant cancer◦ Lesion in femoral bone requiring surgical fixation◦ Serious medical comorbidities precluding RT. These include interstitial lung disease in patients requiring thoracic radiation, Crohn’s disease in patients where the gastrointestinal (GI) tract will receive RT, and connective tissue disorders such as lupus or scleroderma.◦ Substantial overlap with a previously treated radiation volume. Prior RT in general is allowed, as long as the composite plan meets dose constraints herein. For patients treated with conventional radiation previously, similar biologically effective dose calculations should be used to equate previous doses to the tolerance doses listed below. All such cases should be discussed with the local Principal Investigators (PIs) and Sponsor Investigator.◦ Current malignant pleural effusion◦ Liver metastases + planning tumour volume (PTV) located within the “Biliary no fly zone” defined for this trial as the central biliary tract (CBT) (common biliary tract, cystic duct and 1 cm of distal branches) + 1 cm (i.e. CBT + 1 cm = biliary no fly zone)◦ Inability to treat all sites of oligometastatic or oligoprogressive disease◦ Lesions greater than 5 cm outside the brain, except:◦ Bone metastases over 5 cm may be included, if in the opinion of the local PI it can be treated safely (e.g. rib, scapula, pelvis)◦ Any brain metastasis > 3.5 cm in size or a total volume of brain metastases greater than 30 cc◦ Clinical or radiologic evidence of spinal cord compression. Patients can be eligible if surgical resection has been performed.◦ Patients with spine instability as judged by a Spinal Instability Neoplastic Score (SINS) of > 12 [15]◦ Dominant brain metastasis requiring surgical decompression◦ Surgical resection of all metastases (i.e. no lesion available to be treated with SABR)◦ Pregnant or breast feeding

## Pre-treatment evaluation

◦ History and Physical Examination within 6 weeks of study accrual:◦ Including prior cancer therapies and cancer-specific concomitant medications (for example, systemic therapy such as immunotherapy, hormone therapy and/or chemotherapy drugs and regular/supporting medications such as anti-emetics) [14].◦ Re-staging within 8 weeks prior to randomization, and within 12 weeks of treatment:◦ Brain: CT or MRI for tumour sites with propensity for brain metastasis. All patients with brain metastases at enrollment or previously require an MRI.◦ Body: 18-FDG PET/CT imaging is strongly recommended, except for tumours where FDG uptake is not expected (e.g. prostate, renal cell carcinoma). Prostate-specific membrane antigen (PSMA)-PET or choline-PET is recommended for prostate cancer. In situations where a PET scan is unavailable, or for tumours with limited radiotracer uptake, CT chest/abdomen/pelvis with bone scan required. CT neck as clinically indicated.◦ Spine: MRI is required for patients with vertebral or paraspinal metastases, though the MRI can be limited to the involved segment, including at least the involved vertebral body(ies) plus at least one vertebral body above and below, where applicable [14].◦ Pregnancy test for women of child-bearing potential within four weeks of RT start date [14].

### Defining the number of metastases

Patients are eligible if there are 1-5 current oligometastatic lesions present. For oligoprogression, patients can have more than 5 lesions, but only 5 or fewer can be growing, and considered oligoprogressive lesions. Each discrete lesion is counted separately. For patients with lymph node metastases, each node is counted as one site of metastasis. All known metastatic lesions must be targetable on planning CT. For patients where the lesion is only detectable on MRI, fusion of the MRI with the planning CT is required [14].

Patients with prior metastases that have been treated with ablative therapies (e.g. SABR, surgery, radiofrequency ablation) are eligible, as long as those metastases are controlled on imaging. Brain metastases have to have been treated, or will be treated, with ablative technique (surgery, stereotactic radiosurgery [SRS], or stereotactic radiotherapy [SRT]).

When patients have small indeterminate nodules (e.g. a 2 mm lung nodule) it can be difficult to determine whether these are benign or whether they represent metastasis. Any such lesion that is ‘new’ is automatically considered a metastasis unless there are > 2 months of documented stability without systemic therapy [14].

### Brain metastases at presentation

If a patient presents with 1-5 brain metastases and ablation of those metastases (with surgery or radiation) is judged to be clinically required regardless of the treatment of extracranial metastases, ablative treatment is permitted. Those treated metastases count within the total number of five lesions. The patient would then be randomized to treatment of the extracranial disease. For example, a patient with a solitary brain metastasis and two lung metastases could receive an ablative technique to the brain (e.g. surgery, SRS, or fractionated stereotactic radiotherapy [FSRT]), and then be randomized to SF SABR vs. MF SABR for the two lung metastases.

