### 1st randomization

#### Primary endpoint

##### Toxicity

◦ Defined as grade 3-5 adverse events (Common Terminology Criteria for Adverse Events [CTCAE] version 5.0) that are possibly, probably, or definitely related to SABR.

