### Experimental arm – SF SABR (ARM 2)

Patients in the experimental arm will receive SF SABR with doses dependent upon tumour site, as shown in Table 2.

**Table 2 Tab2:** Dose and fractionation in experimental arm (Single Fraction), with [secondary options in square brackets]

**Location**	**Dose (Gy)**	**Fractions**	**Tumour BED (Gy**_**10**_**)**
**Lung** Greater than 2 cm from mediastinum or brachial plexus or if mandatory OAR constraints are met	30 [34]	1	120 [149.6]
Within 2 cm of mediastinum or brachial plexus	20	1	60
**Bone** Any bone	20	1	60
**Liver**	30 [34]	1	120 [149.6]
**Spine**	20	1	60
**Adrenal**	20	1	60
**Lymph node/ soft tissue**	20	1	60
**Brain**	Dose per institutional policy	1	

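### The protocol does not settle whether brain lesions are inside the randomised comparison, and a patient with only brain lesions can enter with no assured fractionation contrast

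*Protocol article*

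**What the plan says.** Four places in the protocol article bear on brain lesions.

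- **Brain metastases at presentation.** Where ablation of 1-5 brain lesions "is judged to be clinically required regardless of the treatment of extracranial metastases, ablative treatment is permitted". Surgery, SRS and fractionated stereotactic radiotherapy are given as examples. "Those treated metastases count within the total number of five lesions". Then: "The patient would then be randomized to treatment of the extracranial disease".
- **Defining the number of metastases.** "Brain metastases have to have been treated, or will be treated, with ablative technique", followed by surgery, SRS or SRT, with no reference to arm.
- **Table 2 (Arm 2, single fraction).** "Patients in the experimental arm will receive SF SABR with doses dependent upon tumour site, as shown in Table 2". Brain is one of the rows: "Dose per institutional policy", with the number of fractions given as 1.
- **Table 1 (Arm 1, multi-fraction).** Brain is again a row, with dose left to the institution and no number of fractions.

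The primary endpoint is grade 3-5 adverse events "that are possibly, probably, or definitely related to SABR". The Primary endpoints section compares them per patient, by worst grade, at any time after treatment. Neither place refers to lesion site or to whether the lesion's fractionation was randomised.

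**The concern.** The first randomisation compares fractionation, so it should be clear for every lesion whether its fractionation is set by the arm. For brain lesions it is not. A centre with an Arm 2 patient cannot tell whether the brain lesion is tied to the single fraction in Table 2 or may have any of the techniques allowed in the section on brain metastases at presentation.

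Two consequences bear on the primary analysis. A patient whose only lesions are in the brain meets the 1-5 count and may be treated alike in either arm. In a non-inferiority trial such patients dilute a true excess and make a false claim of non-inferiority more likely. Separately, if events from brain radiotherapy outside the randomised comparison are counted, they raise the event rate in both arms.

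**Working it through.** **1. The text side by side**

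| Question | Brain metastases at presentation; Defining the number of metastases | Tables 1 and 2 |
|---|---|---|
| Is brain part of the randomised treatment? | No, where ablation is clinically required: only extracranial disease is randomised | Yes: listed in each arm |
| Brain fractionation in Arm 2 | Open | 1 |
| Brain fractionation in Arm 1 | Open | No number given |

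Two other sections treat brain as a trial site. Treatment planning says the sequence should generally begin with the brain, and QA for institutions joining the study names brain among the sites needing a mock plan. The exclusion criteria limit brain lesions by size, total volume and need for decompression, and exclude patients whose metastases have all been resected. None excludes a patient with only brain lesions.

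**2. The plan's own sample size**

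Inputs from the sample size section: 5% in both arms, margin 5 points, one-sided alpha 0.025, power 80%, unpooled z.

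n per arm = [0.05×0.95 + 0.05×0.95] × (1.960 + 0.842)² / 0.05² = 0.095 × 7.849 / 0.0025 = 298.3, so 299 per arm and 598 in total. This reproduces the plan.

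The analysis test named in the protocol is Farrington-Manning. Exact enumeration at 299 per arm gives a false non-inferiority rate of 2.4% at 10% against 5%, and power of 77% at 5% against 5%. Power is below 80% because this test uses a variance restricted to the null.

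**3. Patients with no contrast** (share f is assumed; the article gives none)

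True rates: p₁ = 5% in Arm 1 and p₂ = 0.05f + 0.10(1−f) in Arm 2.

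| f | p₂ | Difference (points) | False non-inferiority, exact Farrington-Manning | Unpooled z approximation |
|---|---|---|---|---|
| 0 | 10.00% | 5.00 | 2.4% | 2.5% |
| 5% | 9.75% | 4.75 | 3.1% | 3.3% |
| 10% | 9.50% | 4.50 | 4.1% | 4.2% |
| 20% | 9.00% | 4.00 | 6.6% | 7.0% |

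Check of the f = 10% row by unpooled z: SE = √[(0.095×0.905 + 0.05×0.95)/299] = 0.02113; (0.05 − 0.045)/0.02113 − 1.960 = −1.723; probability 4.2%.

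**4. Shared brain events in patients who also have randomised lesions**

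Let a share f have brain lesions with grade 3-5 risk b from brain radiotherapy, independent of other events and equal in both arms. With true rates otherwise at 5% and 10%, Arm 1 becomes 0.05 + 0.95fb and Arm 2 becomes 0.10 + 0.90fb. The difference is 0.05(1 − fb).

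For assumed f of 5-30% and b of 2-10%, by unpooled z:

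- the difference is 4.995 to 4.85 points;
- false non-inferiority is 2.51% to 2.88%, against 2.50%;
- power at equal underlying rates is 79.4% to 62.3%, against 80.1%;
- n per arm for 80% power is 304 to 455, against 299.

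If both arms rise from 5% to 6%, exact Farrington-Manning power falls from 77% to 70%. That lift needs fb = 0.01/0.95 = 0.0105, for example f = 20% and b about 5.3%.

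**The case against.** The strongest reply is that the text can be read as two pathways. The section on brain metastases at presentation is conditional: it covers ablation that is clinically required anyway. Other brain lesions could then follow Tables 1 and 2. The references to brain in the treatment sequence and the mock plans fit that reading. So a reader might infer a flat contradiction, and the document does not prove one. What remains is that the two pathways are never spelled out, and the section on defining the number of metastases leaves the technique open for all brain lesions. Even on the two-pathway reading, Table 1 sets no multi-fraction requirement for brain, so a contrast is not assured.

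A reader might also infer that adverse events of non-randomised brain treatment count in the primary endpoint and pull the arms together. The document supports neither half. The endpoint is limited to SABR-related events, so those of brain surgery fall outside it. The two brain sections speak of SRS, SRT or FSRT, while the Background and the arm tables place brain under SABR, so the status of brain radiotherapy events is open. If they count equally in both arms, the working shows that the difference barely moves and the cost is mainly power. If instead Table 2 is followed and Arm 1 policy is fractionated, brain treatment differs by arm.

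The no-contrast share may be small or zero. Under the section on brain metastases at presentation, a patient with only brain lesions has no extracranial disease to randomise and might never be entered. The 5% reference rate comes from SABR-5, and the article does not show whether that rate already includes brain treatment.

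Finally, an article condenses a full protocol, and detailed attribution rules may sit there. That excuses missing detail. It does not reconcile the sections that are printed.

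**Conclusion.** The concern holds in limited form. The sections and tables do not agree on whether brain lesions are inside the randomised comparison. A patient with only brain lesions is not excluded and may have no contrast, and the endpoint leaves open whether events of non-randomised brain radiotherapy count.

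The error-rate inflation in step 3 of the working applies only to patients with no contrast, and its size depends entirely on their assumed share. Shared brain events in other patients are a power problem, and that too depends on an assumed rate. The planned 299 per arm is correct for its stated inputs. The point is worth correcting because the correction is cheap and it protects the primary non-inferiority claim from avoidable dilution.

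**What to change.** 1. Reconcile the sections on defining the number of metastases and on brain metastases at presentation with the brain rows of Tables 1 and 2, so that it is clear which brain lesions, if any, have their fractionation set by the arm. The clinical rule is for the investigators to decide.
2. Require, for entry to the first randomisation, at least one lesion whose fractionation is set by that randomisation.
3. State in the endpoint definition whether adverse events of non-randomised brain treatment count.
4. Keep the per-patient endpoint as primary. Report the result without events attributed to non-randomised brain treatment as a sensitivity analysis. Making lesion-attributed events the primary endpoint would be a doubtful trade: the trial is open-label, knowledge of the arm could influence attribution, and non-focal events are hard to assign to a lesion.

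Cost: a protocol clarification, plus recording whether an event is attributed to non-randomised brain treatment. A few patients with only brain lesions may no longer be randomised.

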### Patients already receiving systemic therapy

If a patient is already receiving systemic therapy, they are still eligible for enrolment. For example, if a patient with four metastases has been on systemic therapy for a year and is planning to continue, they can still be randomized, and will receive SABR (either SF or MF, dependent upon randomization) between cycles, and may require a short treatment break.

## Interventions

### Standard arm – MF SABR (ARM 1)

Patients in the standard arm will receive MF SABR with doses dependent upon the tumour site, as shown in Table 1.

**Table 1 Tab1:** Dose and fractionations in standard of care arm (multi-fraction) by site with [secondary options in square brackets]

**Location**	**Dose (Gy)**	**Fractions**	**Dose per fraction (Gy)**	**Tumour BED (Gy**_**10**_**)**	**Frequency**
**Lung** Greater than 2 cm from mediastinum or brachial plexus or if mandatory OAR constraints are met	48 [54]	4 [3]	12 [18]	105.6 [151.2]	Daily or every second day
Within 2 cm of mediastinum or brachial plexus	60 [50]	8 [5]	7.5 [10]	105 [100]	Daily
**Bone** Any bone except spine	35	5	7	59.5	Daily
**Liver**	54 [50]	3 [5]	18 [10]	151.2 [112.3]	Daily or every second day
**Spine**	24 [35]	2 [5]	12 [7]	52.8 [59.5]	Daily
**Adrenal**	40 [35]	5	8 [7]	72 [59.5]	Daily
**Lymph node/soft tissue**	40 [35]	5	8 [7]	72 [59.5]	Daily
**Brain**	Dose per institutional policy				

### Experimental arm – SF SABR (ARM 2)

Patients in the experimental arm will receive SF SABR with doses dependent upon tumour site, as shown in Table 2.

**Table 2 Tab2:** Dose and fractionation in experimental arm (Single Fraction), with [secondary options in square brackets]

**Location**	**Dose (Gy)**	**Fractions**	**Tumour BED (Gy**_**10**_**)**
**Lung** Greater than 2 cm from mediastinum or brachial plexus or if mandatory OAR constraints are met	30 [34]	1	120 [149.6]
Within 2 cm of mediastinum or brachial plexus	20	1	60
**Bone** Any bone	20	1	60
**Liver**	30 [34]	1	120 [149.6]
**Spine**	20	1	60
**Adrenal**	20	1	60
**Lymph node/ soft tissue**	20	1	60
**Brain**	Dose per institutional policy	1	

### Standard arm – QoL questionnaires only (ARM A)

0-3 days prior to each scheduled patient visit on trial, patients will be prompted to complete the EQ-5D-5L and FACT-G questionnaires [16, 17]. Questionnaire data will be saved in the study database.

### Experimental arm – QoL questionnaires and symptom-specific intervention (ARM B)

0-3 days prior to each scheduled study visit on trial, patients will be automatically prompted to complete the EQ-5D-5L, FACT-G as well as a PRO symptom screen utilizing a generic radiation-related symptom questionnaire. In addition, patients may report symptoms *ad hoc,* with a response by the HCP within three working days. Depending on symptoms entered, patients may receive HCP-guided intervention such as symptom management advice or referral to family physician.

### Immobilization

Treatments will be set up using reproducible positioning and verified using an on-line imaging protocol for all patients in this study. Immobilization may include a custom immobilization device, such as thermoplastic shell or vacuum bag, as per individual institutional practice when delivering SABR. Some institutions do not use immobilization devices and have demonstrated high degrees of accuracy; this is acceptable in this study. Immobilization techniques and devices must not differ between the trial arms.

### Simulation imaging/localization/registration

All patients will undergo planning CT simulation. 4-dimensional (4D) CT will be used for tumours in the lungs, liver, or adrenals, and should be considered for mobile rib lesions. Axial CT images will be obtained throughout the region of interest. The maximum CT slice thickness should be 2.5 mm. The simulation approach for a given site must not differ between trial arms.

### 4D-CT procedures

For patients undergoing 4D-CT for motion management, medical physics will review the 4D-CT images:i)If the quality of the 4D-CT phase bin images is not sufficient, or fails to reconstruct, then untagged average CT and Maximum Intensity Projection (MIP) (± Minimum Intensity Projection (MinIP)) images should be provided for the treatment planning system. Planning will be performed on average CT or 3D helical CT per physics discretion. Physics will assist in assessing the total target motion based on the available scans.ii)Motion assessments in all 3 directions are performed:If the motion is less than or equal to 10 mm, then treatment planning for the motion encompassing method (internal tumour volume [ITV] method) may be performed. Generally, the average CT is used for planning, but planning scan may be a 3D helical per institutional policy.The 50%-60% phase (end expiration) and the 0%-10% phase (end inspiration) should be fused to the planning scan to help define the ITV.If the motion is greater than 10 mm in any one direction, then respiratory-gated or dynamic tumour tracking RT can be considered. Planning CT will be per departmental protocol for the technique selected (generally breath hold exhale scan or 4D-CT 50% phase bin (exhale)).If the motion is greater than 10 mm in any one direction, and respiratory-gated or dynamic tumour tracking RT is not available, ITV method can be considered. Assessing nearby organ at risk (OAR) motion is required and planning at risk volumes (PRVs) applied as appropriate.

### Volume definitions (arms 1 & 2)

For all lesions, the gross tumour volume (GTV) will be defined as the visible tumour on CT and/or MRI imaging ± PET. No additional margin is required for microscopic spread of disease (i.e. clinical target volume [CTV] = GTV) for non-bony lesions). For bone lesions, CTV of 5-10 mm is advised, but 3-5 mm will be allowed upon treating investigator’s discretion. CTV delineation for non-spine bone metastases will be based on consensus recommendations from international experts as published elsewhere [18]. For vertebral lesions, an anatomic approach will be taken as per the International Spinal consortium guidelines [19–21].

An anatomic approach is taken to the CTV based on where the diseases within the spinal segment are located. The rules for CTV are as follows:If the vertebral body is involved with GTV then the entire vertebral body is taken as CTV.If the ipsilateral pedicle and/or transverse process has GTV then the entire ipsilateral posterior segment (pedicle, lamina and transverse process) ± the spinous process is taken into the CTV. The inclusion of the spinous process is per the discretion of the radiation oncologist.If the ipsilateral pedicle, lamina, and/or transverse process has GTV, then the entire ipsilateral posterior segment (pedicle, lamina, and transverse process) plus the spinous process is taken into the CTVIf there is bilateral involvement of the pedicles and/or transverse processes with GTV, then the posterior segment anatomy ± the spinous process is taken into the CTV. The inclusion of the spinous process is per the discretion of the radiation oncologist.If there is bilateral involvement of the pedicles and laminae, and/or transverse processes with GTV, then the entire posterior segment anatomy is taken into the CTV, including the spinous process.If the spinous process is involved with GTV alone then the bilateral lamina ± pedicles are to be taken into the CTV.

The International Spinal Consortium Guideline is a reference for CTV delineation and can be adhered to as they have described [19, 20].

PTV margins of up to 5 mm will be added depending on site of disease, immobilization, and institutional set-up accuracy: 1-3 mm margins may be used for spinal stereotactic treatments, 0-2 mm for brain tumours, and 3-5 mm (dependent on institutional policies) for other sites. PTV margins for a given site must not differ between trial arms.

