## Study design

This is a phase III, investigator-led, open-label, multi-institutional, RCT using a 2x2 factorial design with two randomizations and two primary outcomes. Participating institutions will be tertiary, academic hospitals or RT treatment institutions in Canada, the United Kingdom, United States, and Australia (updated country list available on ClinicalTrials.gov entry NCT05784428). The first and primary randomization is by dose and fractionation, while the second randomization is by HCP-led intervention based on PRO symptom screen, as displayed in schema Fig. 1.

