### Treatment planning

Treatment can be delivered using static beams (either 3D-conformal radiotherapy or intensity-modulated) or rotational therapy (volumetric modulated arc therapy, 3D conformal arcs or tomotherapy). Systematic differences in treatment techniques between trial arms for a particular treatment site are not permitted.

OAR dose constraints may not be exceeded (except chest wall/ribs). If a dose constraint cannot be achieved due to overlap of the target with an OAR, the fractionation (for patients in Arm 1) can be increased, or the target coverage compromised in order to meet the constraint. In cases where the target coverage or dose must be reduced, the priority for dose coverage is the GTV (e.g. attempt to cover as much of the GTV as possible with the prescription dose). All such cases of dose reduction or target coverage compromise must be approved by the local PI prior to treatment.

For patients treated with radiation previously using a different fractionation, similar biologically effective dose calculations should be used to equate previous doses to the tolerance doses listed in Appendix 1 and 2 (with the exception of mean lung dose tolerances, which may be excluded in the context of prior conventionally fractionated radiation doses summed with SABR treatment doses). Equivalent Dose in 2 fractions (EQD2) is the standard radiobiology conversion for overlapping treatment plans contributing to an accumulated dose (sum). An α/β = 2 for cord/brainstem/nerve structures and α/β =3 for all other normal tissues is the current standard.

“Hot Spot” is defined as the dose to 0.035cc volume.

For all targets, doses should be prescribed to either using: 1) the prescription isodose method or 2) the dose-volume method. For prescription isodose method, dose is prescribed to the 60–90% isodose line surrounding the PTV, and all hotspots should fall within the GTV or ITV. For the dose-volume method, ≥ 95% of the PTV should be covered by 100% of the prescription dose, and at least 99% of the PTV should be covered by 90% of the prescription dose. The hot spot should be less than or equal to 150% of the prescription dose (at treating physician’s discretion, up to 167% is acceptable) and should fall within the GTV or ITV.

For spine metastases, it is recommended to keep the hotspots of CTV not including “GTV + 2 mm” to < 110%, to reduce the risk of vertebral compression fracture (VCF).

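### The rule that PTV margins must match across arms does not extend to the bone CTV margin or spinous-process inclusion, which an unblinded physician chooses

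*Protocol article*

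**What the plan says.** Under Study design the article states: "This is a phase III, investigator-led, open-label, multi-institutional, RCT using a 2x2 factorial design". The treating team therefore knows whether a patient is in Arm 1 (multiple fractions, MF) or Arm 2 (single fraction, SF).

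The article guards against arm-dependent planning item by item. It bars between-arm differences in immobilisation, simulation, the approach to organ-at-risk planning margins (PRV), treatment technique, dose algorithm and image guidance. Volume definitions (arms 1 & 2) adds: "PTV margins for a given site must not differ between trial arms".

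The same section leaves two volume choices to the physician with no such clause:

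- Bone lesions: "CTV of 5-10 mm is advised, but 3-5 mm will be allowed upon treating investigator", at that person's discretion. Non-spine bone contours are also to be based on published consensus recommendations.
- Vertebral lesions: six anatomic rules apply. In two of them (one-sided and two-sided involvement of pedicle and/or transverse process), "The inclusion of the spinous process is per the discretion of the radiation oncologist".

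For non-bony lesions the CTV equals the visible tumour (GTV), so this latitude concerns bone only.

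**The concern.** The PTV is the CTV plus a margin. A rule that equalises the outer margin but not the volume beneath it does not equalise what is irradiated. For sites other than spine and brain, the PTV rule controls a range of 3 to 5 mm, a spread of 2 mm. The uncontrolled bone CTV choice runs from 3 to 10 mm, a spread of 7 mm.

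The Background section records concern that single-fraction treatment may be more toxic to nearby organs. A physician who shares it could, within protocol, draw tighter bone CTVs in Arm 2 than in Arm 1. Part of any similarity in grade 3-5 toxicity would then reflect smaller treated volumes, and a cost could appear in lesional control. Randomisation and the stratification factors balance baseline features; they do not protect against a choice made after the arm is known. The opposite tendency is also possible and would count against the single-fraction arm.

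**Working it through.** **1. Is the arm known at contouring?** No sentence gives the timing. Three things point the same way: the trial is open-label; Treatment planning lets fractionation be increased for Arm 1 only when a dose constraint cannot be met, so planning is done with the arm known; and a rule that simulation must not differ by arm would have little purpose if the arm were unknown then. This is an inference.

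**2. How much can treated volume differ?** The article gives no volume figure to reproduce. Inputs from Volume definitions: bone CTV margin 3, 5 or 10 mm; PTV margin 3 mm (low end of 3-5 mm). Assumption: a spherical lesion of diameter d, with no anatomical trimming of the contour.

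PTV volume = (4/3) × π × (d/2 + CTV margin + PTV margin)³

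For d = 20 mm:

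- 3 mm CTV: radius 10 + 3 + 3 = 16 mm, 17.2 cc
- 5 mm CTV: radius 10 + 5 + 3 = 18 mm, 24.4 cc
- 10 mm CTV: radius 10 + 10 + 3 = 23 mm, 51.0 cc

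The ratio of 10 mm to 3 mm is 51.0/17.2 = 2.97. Within the advised 5-10 mm range it is 51.0/24.4 = 2.09.

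The same formula over a range of assumed diameters:

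| Diameter | PTV, 3 mm CTV | PTV, 5 mm CTV | PTV, 10 mm CTV | 10 vs 3 mm | 10 vs 5 mm |
|---|---|---|---|---|---|
| 10 mm | 5.6 cc | 9.2 cc | 24.4 cc | 4.4 | 2.7 |
| 20 mm | 17.2 cc | 24.4 cc | 51.0 cc | 3.0 | 2.1 |
| 30 mm | 38.8 cc | 51.0 cc | 92.0 cc | 2.4 | 1.8 |
| 50 mm | 124.8 cc | 150.5 cc | 229.8 cc | 1.8 | 1.5 |

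**3. How sensitive is the primary test to a shift in rates?** The sample size reproduces: with 5% in both arms, margin 5%, one-sided alpha 0.025 and unpooled variance, n = (1.960 + 0.842)² × 2 × 0.05 × 0.95 / 0.05² ≈ 298.3, so 299 per arm and 598 in total, with power 80.1%.

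Chance of declaring non-inferiority = Φ[(0.05 − (pSF − pMF))/SE − 1.96], where SE = √[(pSF(1 − pSF) + pMF(1 − pMF))/299].

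With pMF = 5%:

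- pSF = 10%: 2.5%
- pSF = 9%: 7.0%
- pSF = 8%: 16.7%

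In the other direction, a rise in pSF from 5% to 6% or 7% lowers power from 80% to 57% or 34%. These 1- and 2-point shifts are assumed. Nothing in the article links CTV margin to a change in event rate or gives the share of patients with bone lesions. The figures show only that the test is sensitive to small shifts, not that contouring would cause one.

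**The case against.** The strongest reply is that the latitude is narrower than it looks. The section applies to both arms, non-spine bone contours follow consensus recommendations, and vertebral contours follow anatomic rules with the spinous process optional in only two of six. Organ-at-risk limits, peer review of every patient, physics checks, mock plans and local approval of coverage compromises all apply. The largest volume ratios compare the two ends of the range in small lesions. The article also condenses a fuller protocol that is not shown.

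Much of this stands as a limit on size. It does not remove the gap. The controls work plan by plan or institution by institution, and none is described as comparing arms. The organ-at-risk limits also exempt chest wall and ribs, so they restrain least where a rib lesion is being contoured. As for condensation, the article states both the discretion and the list of symmetry rules; the point concerns what it fixes.

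A reader might go further and infer that dose option and hot-spot limit should also be equal across arms. The documents do not support that:

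- **Dose option.** Study design says the first randomisation is by dose and fractionation, so dose differs by intent. In Table 2 ("Dose and fractionation in experimental arm (Single Fraction), with [secondary options in square brackets") the only secondary option is 34 Gy instead of 30 Gy, for non-central lung and liver. That is a higher dose, not a retreat by a cautious physician. Non-spine bone has one dose in each arm, so dose option cannot compound the non-spine CTV choice.
- **Hot spot.** Treatment planning sets one limit for both arms (150%; at discretion "up to 167% is acceptable") and places the hot spot within the GTV or ITV. The fracture-related advice concerns CTV outside the GTV plus 2 mm, where a separate level below 110% is recommended. It is not evidence about the 150% to 167% range.

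**Conclusion.** The point holds for bone lesions only. Volume definitions (arms 1 & 2) equalises PTV margins between arms but leaves the non-spine bone CTV margin, and the spinous process in two vertebral rules, to an unblinded physician without a matching clause. Treated bone volume can therefore differ by arm within protocol: about threefold at the extremes for an assumed 2 cm sphere, about twofold within the advised range, and less for larger lesions.

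This rests on the spherical assumption and on the inference that contouring follows allocation. The consequence for grade 3-5 toxicity and lesional control is a reasonable expectation of unknown size. It should not be read as showing that the comparison is biased, or that dose options or hot-spot limits need to match. It is an inexpensive improvement that protects the primary comparison.

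**What to change.** In Volume definitions (arms 1 & 2), extend the sentence on PTV margins so that the approach to CTV margins and to spinous-process inclusion for a given site must not differ systematically between arms. As an alternative, record the intended CTV approach for each bone lesion before randomisation; this also gives a reference against which later departures can be seen.

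As a descriptive check, tabulate PTV volume, dose option and hot-spot level by arm. For the last two this is reporting only, not a requirement of equality.

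The cost is one sentence, or one planning-intent field, plus a table. The downside is slightly less freedom for the physician after allocation; departures for patient safety remain possible if recorded. No margin, dose, hot-spot limit or sample size changes.
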